***Secondary outcomes***

Secondary research goals include an exploration of :

- Percentage of patients in each group that after 12 month achieve one or more of the following targets: HbA1c <6.5% or HbA1c reduction >0.5%; total cholesterol <175 mg/dl; LDL cholesterol <100 mg/dl; HDL cholesterol >40 mg/dl; triglycerides <150 mg/dl; systolic blood pressure (BP) <130 mmHg; diastolic BP <80 mmHg; BMI reduction >1; waist circumference reduction >5 cm.
- Difference between groups in terms of reduction of HbA1c, serum triglyceride and LDL-cholesterol, systolic and diastolic BP, BMI and waist circumference and increment of serum HDL-cholesterol.
- Difference between groups in terms of reduction of number and/or dosage of glucose-, lipid- and BP-lowering drugs.
- Difference between groups in terms of reduction of global cardiovascular 10-year risk (UKPDS risk engine tables).
- Difference between groups in terms of improvement of well-being.
- Difference between groups in terms of direct medical costs and direct and indirect social costs.
- Dose/response relationship between the quality (volume and intensity) of exercise training and modifiable cardiovascular risk factors.
- Relationship between physical fitness at baseline and during the study and modifiable cardiovascular risk factors.

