**Statistical analysis**

***Sample size calculation***

Sample size calculation will be based on the mean HbA1c values (7.6±1.6 %) detected in the SFIDA population, consisting of 11,000 type 2 diabetic patients, aged 46-69 years, a HbA1c reduction of at least 0.5 % in EXE vs. CON group and a statistical power of 90% (α=0.05). To this end, 215 patients per arm need to be enrolled (430 patients total). Assuming a dropout rate of up to 25%, we will recruit 600 patients. Such a sample size also guarantees a statistical power of >90% to detect changes indicated for each of the parameters in the secondary endpoints.

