***Statistical analysis plan***

The c2 test for categorical variables and the Student’s t test or the corresponding nonparametric Mann-Whitney test for continuous variables will be utilized to compare patients’ characteristics at baseline. The efficacy of intervention on primary and secondary endpoints will be assessed using the unpaired t-test or the Mann Whitney U test for continuous variables, by comparing between-groups changes from baseline to end-of-study. For categorical variables (i.e. medications), logistic regression analysis will be applied, with end-of-study rate of use included in the model as the dependent variable and baseline rate of use and study arm included as covariates.

To account for change in medication throughout the 12-month period, multiple regression analysis will be performed, with baseline-to-end-of-study changes as dependent variable and treatment at baseline and treatment initiation during the study as dichotomous variables (yes versus no), whereas drug dosage will not be taken into consideration.

Within group end-of-study vs. baseline values will be compared using the McNemar test for categorical variables and the Wilcoxon signed ranks test for continuous variables. To identify independent predictors of HbA1c changes from baseline, a multiple regression analysis was applied, with mean value of METs, baseline HbA1c values, gender, age, and changes in HOMA-IR, BMI, waist, total, LDL-cholesterol and HDL-cholesterol, and hs-CRP as covariates forced in the model.

Multivariate analysis techniques (multiple or logistic regression) will be used to adjust for differences in the distribution of one or more parameters between the two arms, whereas the ANOVA trend test will be applied for evaluating the relationship of volume and intensity of exercise training (dose/response) and fitness variation with modifiable cardiovascular risk factors.

The likelihood to achieve glycaemic and nonglycaemic targets after 12 months will be estimated using logistic regression, adjusted for baseline status (on-target vs. not-on-target).

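### The claimed power above 90% for every secondary parameter is not supported: the HbA1c responder target has about 80–82% on the sizing assumptions, and the other parameters have no inputs

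*Protocol*

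**What the plan says.** Under Sample size calculation, the protocol sizes the trial on the "mean HbA1c values (7.6±1.6 %) detected in the SFIDA population", with "a HbA1c reduction of at least 0.5 % in EXE vs. CON group and a statistical power of 90% (α=0.05". This leads to "215 patients per arm need to be enrolled (430 patients total", and then "Assuming a dropout rate of up to 25%, we will recruit 600 patients". The paragraph ends: "Such a sample size also guarantees a statistical power of >90% to detect changes indicated for each of the parameters in the secondary endpoints".

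Under Secondary outcomes, the first item is "Percentage of patients in each group that after 12 month achieve one or more of the following targets: HbA1c <6.5% or HbA1c reduction >0.5"%, followed by level targets for total, LDL and HDL cholesterol, triglycerides, and systolic and diastolic BP, and by reduction targets for BMI (more than 1) and waist (more than 5 cm). Later items cover mean differences, drug use, UKPDS risk, well-being, costs and dose/response.

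Under Statistical analysis plan, continuous endpoints are compared as change from baseline. Target attainment "will be estimated using logistic regression, adjusted for baseline status (on-target vs. not-on-target").

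**The concern.** The trial is sized to give just 90% power for a difference in mean HbA1c. Turning a continuous measure into responder or non-responder normally loses information, so a responder endpoint on the same variable, with the same effect and the same patients, should have less power than the mean difference. A guarantee of more than 90% for each secondary parameter therefore looks doubtful for the one target that can be checked. For the rest, the protocol gives nothing to check it with.

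What is at stake is how a null secondary result is read. A reader who trusts the sentence would take a non-significant target comparison as fairly strong evidence against an effect, when the chance of missing the planning effect may be about one in five or unknown.

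**Working it through.** **Inputs from the protocol.** HbA1c mean 7.6, SD 1.6; difference 0.5; power 90%; alpha 0.05 (two-sided reproduces the stated size); 215 per arm; 600 recruited with up to 25% dropout, so 600 × 0.75 = 450, or 225 per arm. Responder: "HbA1c <6.5% or HbA1c reduction >0.5"%.

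**Assumptions not in the protocol.** Baseline and final HbA1c are bivariate normal, each with SD 1.6 and correlation ρ; the control (CON) mean does not change; the exercise (EXE) mean falls by 0.5.

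**Step 1: reproduce the stated size.** n per arm = 2 × (1.960 + 1.282)² × 1.6² / 0.5² = 215.2, against 215 stated. The planned test is on change from baseline, so this treats 1.6 as the SD of change. Power for the mean difference is 90.0% at 215 and 91.2% at 225 per arm.

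**Step 2: implied correlation.** SD of change = 1.6 × √(2(1 − ρ)). Setting this equal to 1.6 gives ρ = 0.5.

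**Step 3: responder rates at ρ = 0.5.** P(responder) = P(final < 6.5) + P(change < −0.5) − P(both).

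- CON: Φ((6.5 − 7.6)/1.6) = 0.2459; Φ(−0.5/1.6) = 0.3773; both 0.1576; total 0.4656.
- EXE: Φ((6.5 − 7.1)/1.6) = 0.3538; Φ(0) = 0.5000; both 0.2540; total 0.5998.
- Difference d: 0.1342.

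**Step 4: power.** Power = Φ[(d√n − 1.96√(2p̄(1 − p̄))) / √(p₁(1 − p₁) + p₂(1 − p₂))], with p̄ = 0.5327.

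At 225 per arm: (0.1342 × 15 − 1.96 × 0.7056) / 0.6992 = 0.90, so power is 81.6%. At 215 it is 79.9%, and at 300 (no dropout) 91.1%. Reaching 90% needs 289 evaluable per arm. Simulating the planned logistic model with baseline on-target status gives 80.3%, 80.4% and 91.1% at 215, 225 and 300.

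**Step 5: sensitivity.**

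| ρ | SD of change | Responder power, 225/arm | Primary power, 225/arm |
|---|---|---|---|
| 0.3 | 1.89 | 71% | 80% |
| 0.5 | 1.60 | 82% | 91% |
| 0.6 | 1.43 | 87% | 96% |
| 0.65 | 1.34 | 90% | 98% |
| 0.7 | 1.24 | 93% | 99% |

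If the CON mean itself falls by 0.25 or 0.5 (ρ = 0.5), responder power at 225 is 81.0% or 79.5%.

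**Step 6: other parameters.** Apart from HbA1c, a size of change is indicated only for BMI and waist, without an SD. The lipid and BP targets are levels without expected rates. Drug use, UKPDS risk, well-being and costs have no indicated change. What can be computed is the detectable difference: solving the Step 4 formula for 90% power at CON rates of 20–50% gives 13.8 to 15.5 percentage points at 215 per arm and 13.5 to 15.2 at 225, so roughly 14–16.

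**The case against.** The best defence has three parts.

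First, the sentence speaks of changes indicated, and the secondary list includes mean differences. For the mean HbA1c difference, power is 90–91%, so on that reading the statement is nearly met (exactly 90% at 215) for the one parameter with inputs. Mean differences of 1 in BMI and 5 cm in waist would also reach 90% at 215 per arm if the SDs of change were no more than about 3.2 and 16 cm (1/0.3126 and 5/0.3126). This stands as far as it goes. But the protocol lists the HbA1c, BMI and waist changes as individual targets to be analysed by logistic regression, gives no SD for BMI or waist, and extends the guarantee to each parameter.

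Second, 1.6 is a cross-sectional population SD and no correlation is stated, so 80% is conditional. That is right, and the range must be shown. It does not rescue the guarantee: the correlation that lifts responder power above 90% also lifts primary power to about 98%, which is not the calculation the protocol reports.

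Third, the secondary goals are described as exploratory and the primary size is sound. Both are true and limit the consequence.

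Two stronger readings are tempting but unsupported.

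- A reader might infer that attaining one or more targets is close to ceiling and cannot separate the arms. No baseline target rates are given. Combining HbA1c below 6.5% (24.6%) with six level targets, 1 − 0.754 × (1 − p)⁶ runs from 60% at p = 10% to 99% at p = 50% under independence, which is itself doubtful for linked lipids and paired BP readings. Entry requires abnormal or treated traits, and the endpoint can be read target by target.
- A reader might infer that baseline on-target status is undefined for HbA1c. It is defined, through the 6.5% limb.

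**Conclusion.** The guarantee is wrong as written. On the reading that reproduces the protocol's own 215 per arm, the HbA1c responder target has about 80% power at 215 and 82% at 225 per arm; it passes 90% only with nearly complete follow-up of all 600 patients or with a correlation of about 0.65 or more. These figures rest on bivariate normality, equal SDs of 1.6 and no control-arm change; across correlations of 0.3 to 0.7 the range at 225 per arm is 71% to 93%. For the other secondary parameters the protocol neither supports nor refutes a power above 90%, because the inputs are absent. None of this implies that the primary comparison is underpowered.

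A minor related point: for the BMI and waist reduction targets nobody can be on target at baseline, so the planned covariate is constant and adjusts for nothing. The comparison stays valid but is unadjusted.

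**What to change.** Remove the guarantee and state the power actually available: about 80–82% for the HbA1c responder target under the sizing assumptions, with the correlation range beside it, and a detectable difference of about 14–16 percentage points at 90% power for a binary target with CON rates of 20–50%. If the sponsor holds SDs or expected rates for particular parameters, state them with the resulting power.

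For the BMI and waist reduction targets, replace the on-target covariate with the continuous baseline value, which is already collected. Keep the on-target adjustment for the level targets and for HbA1c.

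The cost is a few sentences and a less favourable stated power. No extra patients or measurements are needed.

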***Type of randomization***

Patients will be randomized centrally by the use of a permuted-block randomization computer program, stratifying the enrolled subjects by center and, within each center, by age (<60 vs. ≥60 years) and type of diabetes treatment (diet ± oral agents vs. insulin).

***Statistical analysis plan***

The c2 test for categorical variables and the Student’s t test or the corresponding nonparametric Mann-Whitney test for continuous variables will be utilized to compare patients’ characteristics at baseline. The efficacy of intervention on primary and secondary endpoints will be assessed using the unpaired t-test or the Mann Whitney U test for continuous variables, by comparing between-groups changes from baseline to end-of-study. For categorical variables (i.e. medications), logistic regression analysis will be applied, with end-of-study rate of use included in the model as the dependent variable and baseline rate of use and study arm included as covariates.

To account for change in medication throughout the 12-month period, multiple regression analysis will be performed, with baseline-to-end-of-study changes as dependent variable and treatment at baseline and treatment initiation during the study as dichotomous variables (yes versus no), whereas drug dosage will not be taken into consideration.

Within group end-of-study vs. baseline values will be compared using the McNemar test for categorical variables and the Wilcoxon signed ranks test for continuous variables. To identify independent predictors of HbA1c changes from baseline, a multiple regression analysis was applied, with mean value of METs, baseline HbA1c values, gender, age, and changes in HOMA-IR, BMI, waist, total, LDL-cholesterol and HDL-cholesterol, and hs-CRP as covariates forced in the model.

Multivariate analysis techniques (multiple or logistic regression) will be used to adjust for differences in the distribution of one or more parameters between the two arms, whereas the ANOVA trend test will be applied for evaluating the relationship of volume and intensity of exercise training (dose/response) and fitness variation with modifiable cardiovascular risk factors.

The likelihood to achieve glycaemic and nonglycaemic targets after 12 months will be estimated using logistic regression, adjusted for baseline status (on-target vs. not-on-target).

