# **Design and methods**

# **Study design**

# This study is a randomized controlled trial (ISRCTN-04252749). The protocol complies with the Declaration of Helsinki.

**Endpoints**

***Primary outcome***

The primary research goal is the evaluation of the efficacy of a mixed exercise training program, prescribed and supervised, as compared with standard care, in terms of reduction of HbA1c levels.

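### The primary HbA1c comparison is an unadjusted test on change from baseline, sized with the SD of single values; a baseline-adjusted model would be more precise at no cost and free the stated power from an unstated correlation

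*Protocol*

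**What the plan says.** The Primary outcome section compares supervised exercise "as compared with standard care, in terms of reduction of HbA1c levels". The Statistical analysis plan section says that the effect on primary and secondary endpoints "will be assessed using the unpaired t-test or the Mann Whitney U test for continuous variables", and that the quantity compared is the change from baseline to end of study. No covariate enters that comparison.

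The Sample size calculation section rests on the "mean HbA1c values (7.6±1.6 %) detected in the SFIDA population", "a HbA1c reduction of at least 0.5 % in EXE vs. CON group" and "a statistical power of 90% (α=0.05"), and concludes that "215 patients per arm need to be enrolled (430 patients total"). It then allows for up to 25% dropout and recruits 600. It gives no SD of change and no correlation between baseline and 12-month HbA1c.

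The Type of randomization section describes "stratifying the enrolled subjects by center and, within each center, by age" band and type of diabetes treatment. None of these factors appears in the primary comparison. Regression does appear elsewhere in the Statistical analysis plan section. One sentence says that multivariate techniques "will be used to adjust for differences in the distribution of one or more parameters between the two arms". Other models deal with medication changes, predictors of HbA1c change (baseline HbA1c is listed there, study arm is not), medication use adjusted for baseline use, and target attainment adjusted for baseline status.

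**The concern.** The sample size and the test use different variances. The SD of 1.6 describes the spread of one HbA1c value between patients in an outside population. The planned test works on the difference between two values in the same patient. Its SD depends on how strongly they correlate, and the Protocol does not address this. The stated 90% power is therefore a property of the stated test only under an assumption that is not written down.

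Separately, the primary comparison leaves out the covariate most likely to explain 12-month HbA1c, namely baseline HbA1c, and the three factors used to stratify randomisation. The plan already adjusts for baseline in its models of medication use and target attainment, but not for its primary endpoint. At stake are precision and a power statement that holds without an extra assumption. The t-test or Mann-Whitney alternative adds a smaller point: the Mann-Whitney test does not estimate the 0.5-point mean difference on which the trial was sized.

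**Working it through.** **Inputs.** From Sample size calculation: SD 1.6, difference 0.5, power 90%, alpha 0.05, 215 per arm, 600 recruited, dropout up to 25%. Sidedness is not stated; two-sided reproduces the plan's figure and one-sided does not (it gives 176 per arm). Rho is not in the document and is shown as a range. Equal SDs at baseline and 12 months are assumed first and then relaxed.

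**1. The plan's figure.** n per arm = 2 × ((1.960 + 1.282) × 1.6 / 0.5)² = 215.2, which matches the stated 215. The value 1.6 was therefore used directly as the SD of the analysed variable.

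**2. The two variances.** With equal SDs:
- SD of change = 1.6 × √(2(1 − rho)). This equals 1.6 only when 2(1 − rho) = 1, that is, rho = 0.5.
- Residual SD with baseline as covariate (ANCOVA) = 1.6 × √(1 − rho²).
- Ratio of variances, ANCOVA to change = (1 − rho²) / (2(1 − rho)) = (1 + rho)/2.

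**3. Numbers analysed.** 215 per arm as stated; 600 × 0.75 / 2 = 225 per arm at the planned maximum dropout; 300 per arm with none.

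**4. Power.** Power ≈ Φ(0.5 / (SD × √(2/n)) − 1.960). For example, at rho 0.3 and n = 215 the SD of change is 1.893, the standard error is 1.893 × √(2/215) = 0.1826, and 0.5/0.1826 − 1.960 = 0.778, so power is 78%.

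| rho | SD of change | Change, 215 | Change, 225 | Change, 300 | ANCOVA SD | ANCOVA, 215 |
|---|---|---|---|---|---|---|
| 0.3 | 1.893 | 78% | 80% | 90% | 1.526 | 92% |
| 0.4 | 1.753 | 84% | 86% | 94% | 1.466 | 94% |
| 0.5 | 1.600 | 90% | 91% | 97% | 1.386 | 96% |
| 0.6 | 1.431 | 95% | 96% | 99% | 1.280 | 98% |
| 0.7 | 1.239 | 99% | 99% | 99.9% | 1.143 | 99.5% |

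**5. Correlation needed for 90% power with the change-score t-test.** About 0.50 at 215 per arm, 0.48 at 225 and 0.30 at 300. For the Mann-Whitney test under normality (relative efficiency 3/π) the values are 0.52, 0.50 and 0.33.

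**6. Patients per arm for 90% power.** Change score: 215.2 × 2(1 − rho). ANCOVA: 215.2 × (1 − rho²). Rounded up, these are 302 against 196 at rho 0.3, 259 against 181 at 0.4, and 216 against 162 at 0.5.

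**7. Unequal SDs.** Let s be the 12-month SD and keep 1.6 at baseline. The variance of change is 1.6² + s² − 2 × rho × 1.6 × s, which is at most 1.6² when rho ≥ s/3.2. For assumed s of 1.4, 1.2 and 1.0 (none is in the document), the threshold at 215 per arm is 0.44, 0.375 and 0.31. At s = 1.2 and rho 0.3 the SD of change is √(2.56 + 1.44 − 1.152) = 1.688, and power is 87% at 215 per arm and 88% at 225. A 12-month SD above 1.6 would raise the threshold instead.

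**The case against.** The strongest reply is that nothing here shows the trial to be underpowered. A reader might infer that the 90% claim fails unless rho reaches 0.5. The documents do not support that as a general statement. The threshold belongs to exactly 215 analysed per arm and equal SDs at both times. The Protocol recruits 600, which lowers it to about 0.48 at the worst planned dropout and about 0.30 with none, and a narrower spread at 12 months lowers it further. The plan's drug adjustment towards targets in both arms might reduce rho, but it might equally narrow the 12-month spread. The Protocol quantifies neither effect. This reply stands.

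A reader might also infer that leaving out the stratification factors makes the test invalid. It does not. In a randomised trial the t-test on change estimates the mean difference without bias, and ignoring factors balanced by design usually makes the standard error too large. The cost is in power, not in false positives.

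Finally, a reader might infer that the plan permits several primary p-values, because it offers two tests and later mentions adjustment for differences between arms. The text assigns the primary endpoint to the t-test or Mann-Whitney test. It does not say that the later regression replaces that comparison, or that a baseline test triggers it. A rule for choosing between the two tests may properly sit in a statistical analysis plan that is not shown.

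The reply does not remove the efficiency point. The Protocol does not leave the primary test open to adjustment: it names an unadjusted comparison of changes. Under equal SDs that comparison is less precise than ANCOVA at every rho below 1.

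**Conclusion.** The concern holds as a matter of efficiency and of an unstated assumption. The planned primary test is valid, the sample size arithmetic reproduces, and no shortfall in power is proven. However, the stated power carries over to the stated test only if the SD of change is about 1.6 or less at the stated 215 per arm, and the document does not address this.

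Under equal SDs, adjusting for baseline HbA1c cuts the variance to (1 + rho)/2 of the change-score variance: 35% less at rho 0.3, 25% less at 0.5 and 15% less at 0.7. It also holds power at about 90% or more with 215 per arm for any rho of zero or above, provided the 12-month SD does not exceed 1.6. The gain matters most where rho is low or dropout is near the planned maximum, and is small where rho is high. The change is worth making but is not a condition for the trial's validity.

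**What to change.** - Name one primary analysis: a linear model of 12-month central-laboratory HbA1c on study arm, baseline HbA1c, age stratum, diabetes-treatment stratum and centre (fixed or random), reported as an adjusted mean difference with 95% CI.
- Keep the Mann-Whitney test, if wanted, as a sensitivity analysis only.
- State that any adjustment made because of differences between the arms does not replace the primary model.
- In Sample size calculation, say that 1.6 is the SD of single values, and that 215 per arm gives about 90% power or more under this model provided rho is at least zero and the 12-month SD is no more than 1.6.

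The cost is wording only. Baseline and final HbA1c are already measured in the central laboratory, and the stratification factors are recorded at randomisation. No extra patients, visits or measurements are needed.

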# ***Recruitment, randomization and baseline evaluation***

# Patients fulfilling the above criteria will be recruited in 22 outpatients clinics nationwide (see Appendix 1 and Figure 1) and subsequently randomized to two arms:

# mixed (aerobic+ resistance) exercise, prescribed and supervised + exercise counseling (EXE);

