# **Treatments**

***Exercise program***

The training program for the EXE group consists of twice a week supervised sessions of 75 min duration of mixed (aerobic and resistance) exercise, for 12 months.

Aerobic training will be performed using treadmill, step, elliptical, arm or cycle-ergometer. Transformation of maximal oxygen consumption (VO2max)in exercise load will be performed by the use of a software (Wellness System, Technogym SPA, Gambettola, Italy) or a dedicated spreadsheet, which allow calculation of the individual training load for each equipment from VO2max using the American College of Sports Medicine (ACSM) equations [21].

Resistance training will consist of 4 resistance exercises, i.e. thrust movement on the transverse plane (chest press or equivalent), traction movement on the frontal plane (lateral pull down or equivalent), squat movement (leg press or equivalent), trunk flexion for the abdominals, and three stretching positions. Intensity will be adjusted according to improvements in predicted VO2max and 1RM, as recorded throughout the study, thus resulting in further increments of working loads. In addition, caloric expenditure will be increased progressively by 0.1 kcal/kg body weight/session every month (Table 5).

Subjects in the EXE group will be allocated to either moderate-intensity aerobic (at 55% of predicted VO2max) and resistance (at 60% of predicted 1 Repetition Maximum, RM) or high-intensity aerobic (at 70 % of predicted VO2max) and resistance (at 80% of predicted 1RM) exercise, depending on the centres, which have been preliminary assigned to exercise patients at moderate- or high-intensity. Exercise and duration of aerobic training and number of series will be managed to obtain the same caloric expenditure per kg body weight, independent of the intensity level of exercise.

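### The model for independent predictors of HbA1c change forces in mean METs but omits study arm and names no analysis population, so in a pooled fit the METs coefficient can pick up non-volume effects of being in EXE

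*Protocol*

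**What the plan says.** The Statistical analysis plan section describes this regression in one sentence. It opens "To identify independent predictors of HbA1c changes from baseline, a multiple regression analysis was applied, with mean value of METs, baseline HbA1c values, gender, age"; it ends with "changes in HOMA-IR, BMI, waist, total, LDL-cholesterol and HDL-cholesterol, and hs-CRP as covariates forced in the model". That makes eleven forced covariates: mean METs, baseline HbA1c, gender, age and seven changes measured after randomisation. Study arm is not one of them.

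The same section does name arm elsewhere: the logistic model for medications has "baseline rate of use and study arm included as covariates". A later general sentence allows regression adjustment for parameters distributed differently between the arms, but it does not add arm to this model.

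The analysis population is not stated. The sentence just before concerns a different analysis: "Within group end-of-study vs. baseline values will be compared using the McNemar test".

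The arms differ in supervised exercise by design. The EXE arm is defined as "mixed (aerobic+ resistance) exercise, prescribed and supervised + exercise counseling (EXE"), and the Exercise program section says "The training program for the EXE group consists of twice a week supervised sessions of 75 min duration". Table 5 raises planned expenditure from 3.0 kcal/kg per session in month 1 to 4.1 in month 12.

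**The concern.** METs are partly a marker of arm. The Exercise program section also plans the same caloric expenditure per kg whatever the intensity level, so attendance aside, the main planned contrast in supervised volume is EXE against CON.

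If both arms are fitted together without an arm term, the randomised contrast itself counts as evidence on METs. Any benefit of EXE that reaches HbA1c by a route other than volume, and other than the seven listed changes, is then credited to METs. Supervision and regular contact with staff are the clearest candidates. A trial that succeeds on its primary endpoint would be more likely to report METs as an independent predictor, even if patients who exercised more within their arm did no better.

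**Working it through.** **The plan's own figures.** No figure is given for this regression, so the check starts from the Sample size calculation section (difference 0.5, SD 1.6, power 90%, α 0.05).

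- n per arm = 2 × (1.96 + 1.2816)² × 1.6² / 0.5² = 215.2. This is 216 rounded up, against 215 stated; power at 215 is 89.97%. The figure reproduces as two-sided.
- Completers: 600 × (1 − 0.25) = 450.

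**Separation of METs by arm.** The Table 5 mean is (3.0 + 4.1)/2 = 3.55 kcal/kg per session. Two sessions a week give d = 7.1 kcal/kg per week, ranging from 6.0 in month 1 to 8.2 in month 12.

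**Assumptions not in the protocol.** 1 kcal/kg is about 1 MET-h; attendance is full; unsupervised activity is equal in both arms; the baseline-to-final HbA1c correlation is 0.5; the within-arm SD of METs, s, is 4 to 30 MET-h/week. Volume has no effect within arm, and the arm effect is Δ = 0.5%.

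**Model without arm, no mediation.** With 1:1 allocation:

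- Variance of METs: V = s² + d²/4 = s² + 12.60
- Spurious METs coefficient (absolute value): b = Δ(d/4)/V = 0.8875/V
- Residual SD: σ = √[1.6²(1 − 0.5²) + (Δ²/4)(1 − 12.60/V)]
- z = b√(450V)/σ; rejection rate = Φ(z − 1.96) + Φ(−z − 1.96)

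For s = 4: V = 28.60, b = 0.0310, σ = 1.398, z = 2.52, rejection 71%. For s = 10: V = 112.60, b = 0.0079, σ = 1.406, z = 1.26, rejection 24%.

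**Simulation of the listed eleven-covariate model** (3,000 trials per setting, N = 450). In the mediation columns, one forced change covariate is shifted by 0.5 SD in EXE and carries half or all of the arm effect.

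| s | Formula, no mediation | Simulated, no mediation | Half mediated | Fully mediated |
|---|---|---|---|---|
| 4 | 71% | 71% | 22% | 5% |
| 6 | 49% | 47% | 15% | 5% |
| 8 | 33% | 31% | 10% | 5% |
| 10 | 24% | 24% | 9% | 5% |
| 15 | 14% | 13% | 8% | 5% |
| 20 | 10% | 11% | 6% | 6% |
| 30 | 7% | 8% | 6% | 4% |

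With study arm added, the METs rejection rate was between 4% and 6% in every setting.

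**Sensitivity to attendance.** At an assumed 80% attendance (d = 5.68), the unmediated rates for s = 4, 6, 8 and 10 fall to 58%, 37%, 23% and 18%.

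**The case against.** Several points on the other side stand.

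- **Pooling is inferred.** No population is named, and the preceding sentence concerns within-group comparisons. If the model is fitted within each arm, the problem disappears. Still, nothing restricts the sentence to one arm, and its stated aim is predictors of HbA1c change in general, so pooling remains the more natural reading.
- **METs is one covariate of eleven.** No hypothesis about volume is stated for this model. Dose-response is a separate secondary goal with its own ANOVA trend test. A reader might infer that this regression is the trial's volume-response analysis; the protocol does not give it that role.
- **Not every difference between arms is a non-volume route.** Drug adjustment is prescribed for all patients, and working to common targets would tend to shrink an arm difference in HbA1c. Resistance work enters the volume count at 3 METs/hour, so it is at least partly captured. Counseling goes to both arms. Supervision and session contact remain.
- **The scenario is an extreme one.** It sets the within-arm volume effect to zero. If the whole arm effect runs through volume, omitting arm does not bias METs by this route, and adding arm discards valid between-arm information.
- **The SD of METs drives the result and is not given.** The diary also records occupational, commuting and home activities. Housework is 3.5 METs in Table 4, so ten hours a week is 35 MET-h. If such activity enters the mean METs, an SD well above 10 is plausible and the unmediated rate falls to between 7% and 14%.

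These points limit the size of the problem and the certainty that it arises. They do not make the model without arm suitable for calling METs independent.

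**Conclusion.** The concern holds in limited form. The protocol fixes a covariate list that omits arm while including a variable that differs by arm by design, and it does not say who is in the model. In a pooled fit, METs can be declared an independent predictor with no within-arm volume effect. The chance ranges from close to the nominal 5% up to about 70%, depending on the spread of METs and on how much of the arm effect passes through the forced changes. The upper end needs a small METs SD, full attendance and no mediation.

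It would be too strong to say that METs will come out significant whenever the primary endpoint succeeds. That requires an EXE effect outside both volume and the listed changes, and even then rejection is far from certain. The analysis is exploratory, and the primary between-arm comparison and the sample size are untouched. The change is worth making because it is cheap and removes an ambiguous claim.

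**What to change.** State that the model is fitted in both arms together, with study arm added to the forced covariates, or that it is fitted separately within each arm. Call METs an independent predictor only on the basis of that model, and show the model without arm as descriptive.

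This takes one sentence and one model term, and needs no new data. The cost is a wider interval for METs, because the between-arm contrast no longer counts as evidence on volume. Two cautions belong with it. The within-arm METs association remains observational, since volume within arm is not randomised. The arm coefficient in this model is adjusted for changes after randomisation, so it should not be read as the treatment effect.
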